### Participant timeline {13}

A schematic overview of study visits and assessments is shown in Table 1. The total duration of the study will be the undefined period of time between screening and the start of the investigative product and 12 months of follow-up.

**Table 1 Tab1:**
[figure not shown]
The schedule of enrolment, interventions and assessments in the Standard Protocol Items: Recommendations for Interventional Trials (SPIRIT) figure

* AUC* area under the curve, *MMF* mycophenolate mofetil, *TAC* tacrolimus

### Sample size {14}

A sample size calculation is based on the log-rank test for comparing two groups, a follow-up of 12 months and the assumption of exponential survival times. The expected difference between groups was formulated in terms of relative risk derived from the expected cumulative incidences in the two groups according to previous literature. Papers on MMF for insufficient response in EU and North America reported 13%, 21% and 34% CR respectively, and review of the literature on TAC in adult AIH patients was also taken into account [22, 23, 25, 36]. Assuming proportions of CR at the end of follow-up of 0.22 in the MMF group and 0.53 in the TAC group with a two-sided *α* of 0.05 significance level and power of 1 − *β* = 0.8 to determine the difference in proportions of 0.31, results, in *N* = 38 patients per group. Taking into account a 10% loss to follow-up (e.g. due to side effects), this results in *N* = 43 patients per group. Thus, we aim to include a total of 86 patients.

### Recruitment {15}

Recruitment will take place at regular outpatient clinic visits. Patients will be approached by their treating physician. Study visits will take place during regular outpatient clinic visits, providing a low threshold for participation in follow-up.

#### Concealment mechanism {16b}

Participants, treating physicians and local and central study coordinators are blinded for the randomisation process, but not for medication use during the study (because of the need for blood level monitoring of TAC) and not for the outcome of individual participants.

#### Implementation {16c}

Randomisation will be done by the central study coordinator. Assessors of the final outcome will be blinded. The allocation sequence is unknown to the central study coordinator.

### Assignment of interventions: blinding

#### Who will be blinded {17a}

The design of this study is open-label. This entails that only the outcome assessors will be blinded during analyses. The assigned study arm will be known for both patients and all research staff (including the primary caregiver and principal investigator).

#### Procedure for unblinding if needed {17b}

As this is an open-label study, unblinding of participants, local and central study coordinators and primary caregiver will not be required.

### Data collection and management

#### Plans for assessment and collection of outcomes {18a}

At the screening visit, data on demographics, medical history and medication use is collected after obtaining informed consent. Simultaneously laboratory assessments are done, including screening for systemic infections and pharmacogenetics, and VCTE is performed. After inclusion, participants visit the outpatient at different timepoints (Table 1). During these visits, laboratory tests are done, TDM is done using the area under the curve measurements (visits T_2_ and T_12_) or trough levels (only for TAC on visits T_24_, T_36_, T_52_), and (serious) adverse events ((S)AEs) are reviewed. During specified study visits, health-related quality of life (HRQoL) questionnaires are administered and VCTE is done.

#### Plans to promote participant retention and complete follow-up {18b}

Participants visit the outpatient clinic at an interval of 3 months, as per the standard of care in most participating centre. Patients who are referred from a recruiting centre can visit the participating centre at a six-monthly interval, having the remaining study visits in the recruiting centre as part of standard care. For patients who withdraw from the study due to (severe) side effects of toxicity, follow-up visits will be performed with the exception of TDM. No additional data of patients discontinuing treatment for other reasons will be collected.

#### Data management {19}

All data will be entered electronically in case report forms in Castor EDC. Data are collected by the site personnel or the coordinating investigator. After signing informed consent, participants will receive a trial identification number.

#### Confidentiality {27}

All data and specimens will be entered and stored in a coded fashion. The code key will be kept at the participating sites. Access will be limited to involved researchers, who are responsible for the processing of the data. The dataset analysed during the current study and statistical code can be requested through the principal investigator of the sponsor site.

#### Plans for collection, laboratory evaluation and storage of biological specimens for genetic or molecular analysis in this trial/future use {33}

At screening, weeks 24 and 52, additional serum samples will be taken for central end-point analyses. All biological specimens stored during the study are stored for possible additional analyses at a later stage.

### Statistical methods

#### Statistical methods for primary and secondary outcomes {20a}

Intention-to-treat analysis will be used throughout the study for primary and secondary endpoints. All randomised patients will be included in the intention-to-treat analysis. CR at 12 months will be reported as percentage. A Kaplan–Meier survival analysis with log-rank test will be performed to assess the rapidity of reaching CR. Time to CR will be censored at 12 months. In the unlikely event that a subject is withdrawn from the study due to liver-related mortality or liver transplantation, a competing risk analysis according to Fine and Gray will be performed.

All parameters will be summarised by the treatment group using descriptive statistics. Mean, standard deviation, median and range will be used for continuous variables. Counts and percentages will be used for categorical variables. For normally distributed continuous variables, Student’s *T*-test will be used, for not normally distributed continuous variables Mann–Whitney *U* test will be used. For categorical variables, the chi-square test or Fisher exact test will be used. For repeated measurements, paired *T*-test and Wilcoxon signed rank test will be used where appropriate. Confounding will be tested where appropriate.

The economic evaluation comparing the MMF and TAC policies will include a trial-based cost-effectiveness analysis (1-year healthcare costs per complete biochemical remission) and a model-based cost-utility analysis (life-long societal costs per QALY, calculated from the EQ-5D-5L).

Statistical analyses will be performed with Statistical Package for Social Sciences (SPSS), version 24.0 or higher. Two-sided tests will be used and* p*-values < 0.05 will be deemed significant.

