#### Relevant concomitant care permitted or prohibited during the trial {11d}

New medication may be prescribed at the discretion of the treating physician. No new immunosuppressants may be used, besides the corticosteroids already in use at screening. If a flare of AIH (ALT > 10 × ULN) occurs during the study period, patients will receive the standard of care from the treating physician and trial participation will end. Study subjects are not allowed to participate in other trials investigating pharmaceutical agents for AIH.

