#### Secondary outcomes

The secondary objectives are:Safety and tolerability—number and severity of side effects; rate of stopping treatment due to side effects; serum creatinine and potassium; blood pressure; blood glucose levels and incidence of new-onset diabetes; number of (opportunistic) infections; tremor; diarrhoeaProportion of patients with CR after 6 monthsCumulative corticosteroid doseChange of AST, ALT and IgG at 6 and 12 months versus baseline and between groups at the same time pointsLiver function: total bilirubin, albumin, INR and MELD-score after 6 and 12 months between groupsFibrosis: liver stiffness as measured by elastography and blood fibrosis markers (Enhanced Liver Fibrosis test)Quality of life (questionnaires) using the validated liver disease symptom index (LDSI), short-form 36 (SF-36) and EQ5DCost-effectiveness: using modified Productivity Cost Questionnaire (iPCQ) and Medical Consumption Questionnaire (iMCQ) questionnaires

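### Secondary outcomes that accumulate with time are compared by tests that ignore observed time, although observation can end early at a flare or other exit

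*Protocol article*

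**What the plan says.** The list of secondary outcomes in section {12} includes several that build up over follow-up: number of side effects, "number of (opportunistic) infections", new-onset diabetes and cumulative corticosteroid dose. Section {20a} adds a trial-based economic analysis of "1-year healthcare costs per complete biochemical remission".

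Section {20a} covers primary and secondary outcomes. For comparing arms on continuous variables it names the t-test or the Mann–Whitney test. For the rest, "For categorical variables, the chi-square test or Fisher exact test will be used". Methods that use follow-up time (Kaplan–Meier, log-rank, Fine and Gray) appear there only in connection with complete biochemical response (CR). Section {20c} says missing data will be handled by additional analyses, with imputation as an example.

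Three sections govern how long a patient is observed:

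- {11d}, at a flare: "patients will receive the standard of care from the treating physician and trial participation will end".
- {18b}: patients who stop because of side effects keep their visits apart from drug monitoring, but "No additional data of patients discontinuing treatment for other reasons will be collected".
- {11b}: visits and assessments continue whenever study medication is discontinued, with no reason excepted. The same section says subjects may leave at any point, and makes withdrawal at a flare a decision of the investigator.

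**The concern.** A count or a running total means the same thing in both arms only if patients are observed for equally long. Here observation can stop early, and one of the stopping events, a flare, is itself a treatment failure. A patient who leaves at month 3 contributes three months of infections, steroid use and cost; one who stays contributes twelve. None of the tests named for these outcomes takes this into account. Early exit is then scored as few infections, a low steroid dose and low cost.

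Safety, steroid use and cost are what will be set against the CR result when one drug is preferred to the other. Section {6b} already frames the choice as a possible trade of efficacy against adverse effects.

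**Working it through.** **Inputs from the document.** Section {14}: "Assuming proportions of CR at the end of follow-up of 0.22 in the MMF group and 0.53 in the TAC group", two-sided alpha 0.05, power 0.80, 38 per group, 10% loss to follow-up, 43 per group, 86 in total. Section {14} does not split the loss by arm. The reason it offers as an example is side effects, which under {18b} would not end observation. The 10% is therefore only a yardstick for the exits that matter here.

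**The plan's own figure.** The two-proportion formula with pooled variance gives

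n = [1.96·√(2·0.375·0.625) + 0.842·√(0.22·0.78 + 0.53·0.47)]² / 0.31² = (1.342 + 0.546)² / 0.0961 ≈ 37.1, hence 38.

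Then 38/0.90 = 42.2, hence 43 per arm. The sample size reproduces with this formula, and nothing below changes it.

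**Effect of unequal exit on a raw count.** Assume the same true event rate in both arms, a share f of an arm exiting, and exit on average at month t. Observed years per patient are 1 − f(1 − t/12). Exits spread evenly over the year correspond to t = 6. All values of f and t are assumptions.

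| Exits, arm A vs arm B | Mean exit month | Observed years, A vs B | Raw count in B |
|---|---|---|---|
| 0% vs 10% | 6 | 1.000 vs 0.950 | 5% lower |
| 5% vs 15% | 6 | 0.975 vs 0.925 | 5% lower |
| 5% vs 15% | 4 | 0.967 vs 0.900 | 7% lower |
| 0% vs 20% | 6 | 1.000 vs 0.900 | 10% lower |
| 0% vs 20% | 4 | 1.000 vs 0.867 | 13% lower |

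The last four rows all average 10% overall. The 0% vs 20% rows are the extreme in which the whole planned loss falls in one arm: 0.10 × 86 = 8.6 patients, and 8.6/43 = 20%. At one event per patient-year, 0% vs 20% at mean month 6 gives 43.0 vs 43 × 0.900 = 38.7 events from identical true rates.

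**False-positive rate on a total.** I simulated 43 per arm with equal, constant true daily doses (coefficient of variation 0.4) and exits uniform over 12 months. The t-test and Mann–Whitney test on totals reject in 8–9% of trials at 10% vs 0%, and in 19–20% at 20% vs 0%, against a nominal 5%.

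**Steroids when dose depends on response.** Assume 10 mg/day all year without CR (3.65 g), half that from month 6 with CR (0.75 × 3.65 = 2.74 g), and exits at month 6 among those without CR (1.825 g unobserved each).

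- Complete follow-up: TAC 0.53 × 2.74 + 0.47 × 3.65 = 3.17 g; MMF 0.22 × 2.74 + 0.78 × 3.65 = 3.45 g.
- Exits 5% TAC, 15% MMF: 3.17 − 0.05 × 1.825 = 3.08 g vs 3.45 − 0.15 × 1.825 = 3.18 g. The difference shrinks.
- Exits 5% vs 25%: 3.08 vs 2.99 g. The order reverses, but overall exit is then 15%, above the planned loss.

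**Is dose per observed day a remedy?** Only if dose is constant. Suppose both arms truly follow the same course, with dose halved from month 6. A completer's mean is 0.75 of the starting dose. A patient exiting uniformly over the year averages 0.5 + 0.25 + 0.25·ln 2 = 0.923.

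- Exits 10% vs 0%: 0.90 × 0.75 + 0.10 × 0.923 = 0.767, against 0.750: 2% too high in the arm with more exits.
- Exits 30% vs 5%: 0.70 × 0.75 + 0.30 × 0.923 = 0.802, against 0.95 × 0.75 + 0.05 × 0.923 = 0.759: 6% too high, with about 9% false positives in simulation.

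The bias changes sign but does not go away.

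**The case against.** The strongest reply is that {20a} is a generic list of tests. It assigns no test to steroid dose, infections or costs, and never says that totals will be left unadjusted. Person-time denominators and censored-cost methods often sit in an analysis plan or economic plan, neither of which is shown, and {20c} leaves room for imputation. This stands against any claim that the protocol commits to raw totals. It does not dispose of the point. The section does name methods for secondary outcomes, and it uses time for CR but not for these. {20c} names no method and does not say that a count or total cut short by exit is treated as missing. No later plan can recover data that were never collected.

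A reader might go further and infer that MMF, with its lower expected CR, will look safer and more steroid-sparing. The document does not support that:

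- Failing to reach CR is not an exit criterion. Under {11b} a smaller rise in ALT leads to a change in steroid dose while participation can continue.
- No exit rate by arm is given.
- Patients who stop because of side effects stay under observation, so the shortfall comes only from flares and other exits.
- Exit shares of 20–30% in one arm with 5–10% in the other give larger distortions, but they exceed the planned 10% loss overall.
- For steroids, the arm with more failures may also use more while observed.

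**Conclusion.** The point holds in conditional form. Observation is tied in part to treatment failure, and the tests named for accumulating outcomes do not use observed time. If flares and other non-toxicity exits differ between arms, unadjusted counts and totals are understated in the arm with more of them. The size is about 5% at 10% versus 0% exits, and about 10% (13% if exits come early) if the whole planned loss fell in one arm. These figures rest on assumed exit rates and timing and on equal true event rates. For cumulative steroid dose the likelier result within the planned loss is a true difference that is diluted, not reversed. The primary endpoint and the total of 86 are unaffected. The change is worth making because it is inexpensive and these outcomes will be weighed against CR.

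**What to change.** In {20a}:

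- Analyse side effects and infections as rates: negative binomial regression, or Poisson with robust standard errors, with log observed time as offset.
- Analyse new-onset diabetes as cumulative incidence over time instead of a raw percentage.
- Keep the 12-month total as the outcome for steroid dose and 1-year costs. State how early exit is handled: inverse-probability-of-censoring weighting, or multiple imputation by interval. Do not substitute a simple dose per observed day.
- Report person-time and exits by reason for each arm beside these tables.

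Reconcile {11b}, {11d} and {18b} on which data are collected after a flare, after stopping study medication and after leaving the trial. The analysis methods depend on the answer, and weighting or imputation only partly replaces data that are not collected.

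The cost is protocol or analysis-plan wording, somewhat more analysis work and tables that are less simple to read. With 5 of 86 patients randomised at the time of the article, settling the data-collection question early would benefit nearly the whole trial.

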### Eligibility criteria {10}

#### Inclusion criteria

Patient is older than 18 years old.Probable or definite auto-immune hepatitis according to the original or simplified IAIHG criteria (> 10 points pre-treatment on the original criteria or > 6 points on the simplified criteria) [1, 2].Incomplete responder on at least a half year of first-line treatment, including azathioprine/6-MP/6-TG and prednisolone or budesonide.ALT 1.5–10 × ULN for at least 2 months.Patient is capable of understanding the purpose and risks of the study, has been fully informed and has given written informed consent to participate in the study.

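### The continuous secondary outcomes have no baseline-adjusted comparison between tacrolimus and mycophenolate, which costs precision

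*Protocol article*

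**What the plan says.** The article's section on statistical methods ({20a}) assigns tests by type of variable. For comparing continuous variables it says "For normally distributed continuous variables, Student’s *T*-test will be used" and "for not normally distributed continuous variables Mann–Whitney *U* test will be used". For serial data it says "For repeated measurements, paired *T*-test and Wilcoxon signed rank test will be used where appropriate". The only mention of anything like adjustment is "Confounding will be tested where appropriate", with no covariate, outcome or model attached.

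The Secondary outcomes section has two aims for AST, ALT and IgG: movement from baseline to months 6 and 12, and a comparison of the arms at those times. For bilirubin, albumin, INR and MELD it gives only a comparison of the arms at 6 and 12 months. For liver stiffness, fibrosis markers and quality of life it states neither a contrast nor a time point.

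Baseline data exist. Of the screening visit, section {18a} says: "Simultaneously laboratory assessments are done, including screening for systemic infections and pharmacogenetics, and VCTE is performed". Later measurements exist too: "During specified study visits, health-related quality of life (HRQoL) questionnaires are administered and VCTE is done", and in section {18b}, "Participants visit the outpatient clinic at an interval of 3 months". Section {16a} stratifies randomisation by cirrhosis, defined by elastography or biopsy.

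**The concern.** A t-test or Mann–Whitney test between arms has no place for a covariate. If it is applied to follow-up values, differences between patients that were already present at entry stay in the error term. Those differences may be large for ALT, where the entry criterion is "ALT 1.5–10 × ULN for at least 2 months", a range of 10/1.5 = 6.7-fold. If it is applied to changes, the baseline is used, but with a fixed weight of one in place of the weight that the data support. Measurement noise at baseline is then added to the outcome. In neither case is the cirrhosis stratum used, although cirrhosis may be defined by the same elastography that yields the stiffness outcome.

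The paired tests do not fill the gap, because they describe each arm against itself. Patients enter with raised ALT, so some fall in both arms is plausible from regression to the mean alone. A paired p-value in each arm therefore says nothing direct about TAC against MMF.

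At stake is how precisely the trial can describe differences in enzymes, IgG, liver function, stiffness and quality of life with about 40 patients per arm.

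**Working it through.** **The plan's own figure.** The article gives no sample size, standard deviation or correlation for a continuous outcome. The figure it does give, from section {14}, sets the number of patients per arm. With proportions 0.22 and 0.53 (mean 0.375), two-sided α = 0.05 and power 0.80, the two-proportion formula gives

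n = [1.960·√(2·0.375·0.625) + 0.842·√(0.22·0.78 + 0.53·0.47)]² / 0.31² = (1.342 + 0.546)² / 0.0961 ≈ 37.1, so 38 per arm.

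Then 38/0.90 = 42.2, so 43 per arm and 86 in total, as stated. The 38 evaluable patients per arm are used below.

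**Variance of the arm difference.** Let r be the correlation between baseline and follow-up, and assume the same standard deviation (SD) at both times. In units of that variance, the per-patient variance is:

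- follow-up value only: 1
- change from baseline: 2(1 − r)
- analysis of covariance (ANCOVA): 1 − r²

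The ratio of ANCOVA to follow-up-only is 1 − r². The ratio of ANCOVA to change score is (1 − r²)/[2(1 − r)] = (1 + r)/2. Both are below 1 for any r strictly between 0 and 1.

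| r (assumed) | ANCOVA / follow-up only | ANCOVA / change score |
|---|---|---|
| 0.3 | 0.91 | 0.65 |
| 0.5 | 0.75 | 0.75 |
| 0.7 | 0.51 | 0.85 |

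**What this means with 38 per arm.** The difference detectable with 80% power is (1.960 + 0.842)·√(2/38)·√variance = 0.643·√variance, in SD units. Power is for a true difference of 0.5 SD.

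| r | Detectable: follow-up / change / ANCOVA | Power: follow-up / change / ANCOVA |
|---|---|---|
| 0.3 | 0.64 / 0.76 / 0.61 | 59% / 45% / 63% |
| 0.5 | 0.64 / 0.64 / 0.56 | 59% / 59% / 71% |
| 0.7 | 0.64 / 0.50 / 0.46 | 59% / 80% / 86% |

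**Without equal variances.** Let the SDs be s_b at baseline and s_f at follow-up. The change-score variance is s_f² + s_b² − 2r·s_b·s_f, and the ANCOVA variance is s_f²(1 − r²). Their difference is (s_b − r·s_f)², which is never negative. The direction therefore does not depend on equal variances, but the sizes in the (1 + r)/2 column do. The 1 − r² column does not.

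**Why paired tests cannot stand in for the comparison.** Suppose both arms truly change by the same amount and each paired test has power p. One arm is then significant and the other not with probability 2p(1 − p): 2·0.8·0.2 = 0.32 at 80% power and 2·0.5·0.5 = 0.50 at 50% power.

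**The case against.** The strongest reply is that the plan does what its objectives ask. The Secondary outcomes section has two aims for AST, ALT and IgG. The paired tests serve the one against baseline, and the t-test or Mann–Whitney test serves the one between arms. This stands: the paired tests are not wrong for their own purpose. A reader might infer that within-arm p-values are to be used to claim a difference between TAC and MMF, but no sentence in the article says so. The 32% to 50% above shows why that inference should be ruled out; it does not show that it is planned.

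A reader might also infer that the baseline is thrown away. The article does not support that either. The paired tests use it, and the wording for AST, ALT and IgG allows the arms to be compared on changes. Nor is a change from baseline stated for liver function, stiffness or quality of life.

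It can be said that the sentence on confounding, together with an analysis plan not shown here, leaves room for adjustment. This stands only in part. That sentence names no covariate and no model, while the unadjusted tests are named outright. An analysis plan would have to replace this text, not merely complete it.

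Finally, the size is hypothetical. The correlation is assumed, equal variances are doubtful for ALT when treatment aims at normal values, and the formulas do not apply directly to Mann–Whitney. At r = 0.3 the gain over a follow-up-only comparison is only 9%. All of this is fair as to size, but the direction holds for mean comparisons.

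**Conclusion.** The point holds as one of efficiency. For the continuous secondary outcomes the article fixes unadjusted between-arm tests and within-patient paired tests, and names no baseline-adjusted arm difference, although baseline values are collected and cirrhosis is the stratification factor.

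Under equal variances and an assumed correlation of 0.3 to 0.7, the named tests forgo a variance reduction of 9% to 49% if follow-up values are compared, or of 35% to 15% if changes are compared. Which applies cannot be settled, because the article allows either reading for AST, ALT and IgG.

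The point goes no further. Unadjusted comparisons are valid under randomisation with complete data, so no bias is shown. A reader might take the lost precision to mean that the trial is too small, but the 86 patients rest on the primary endpoint and no power is claimed for secondary outcomes. How many repeated measurements of stiffness and quality of life go unused cannot be judged, because the visit table is not visible.

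**What to change.** For each continuous secondary outcome with a baseline value, state that the arms are compared by ANCOVA at 6 and 12 months, or by a mixed model for repeated measures with arm, visit and arm-by-visit terms. In either case adjust for the baseline value and the cirrhosis stratum. Analyse skewed variables such as ALT and AST on the log scale; this also avoids letting the observed distribution decide which quantity is compared. Report the arm difference with its 95% confidence interval at both times.

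Keep the within-arm comparisons descriptive, and state that they will not be used to infer a difference between TAC and MMF.

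The cost is a paragraph of analysis wording and a little analysis work, feasible in the named software. No new visits, measurements or patients are needed. With 5 of 86 patients randomised at publication, the change could be made before outcomes are known.
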